### Data Management

Information from the hypertension registry and the randomization table was loaded into REDCap electronic data capture tools hosted at Kaiser Permanente Colorado. REDCap was then used for study data collection, data management, and completion of the study visit questionnaires. REDCap is a secure, Web-based app designed to support data capture for research studies, providing (1) an intuitive interface for validated data entry, (2) audit trails for tracking data manipulation and export procedures, (3) automated export procedures for seamless data downloads to common statistical packages, and (4) procedures for importing data from external sources [44].

### Analysis Plan

The primary analytic strategy will be intention to treat. As secondary analyses, we will also perform per protocol and as-treated analyses. Linear mixed models will be used to analyze repeated measures of systolic blood pressure (the primary outcome variable) and diastolic blood pressure (a secondary outcome variable) as continuous variables [45]. For each group, the changes from baseline at 6 and 12 months after randomization can be obtained after the linear mixed model is fit and all coefficients are estimated. Then, we will contrast the changes from baseline between the 2 groups to assess the influence of IVR-T intervention on systolic blood pressure and diastolic blood pressure. We also plan to analyze the secondary outcomes missed appointment and medication adherence status using nonlinear mixed models.

We anticipate that some outcomes will be missing because of missed appointments or attrition. By default, the linear mixed models accommodate missing data by assuming that data are missing at random (MAR). We will explore different ways to examine the assumption of MAR [46]. When the data are missing not at random, outcome measures and missingness will be jointly modeled with either random effects selection models or pattern mixture models, whichever is appropriate [47,48]. Multiple imputation methods will also be used to explore the sensitivity of the results to missingness [49].

In our analyses of the baseline data, we compared individuals in the recruitment pool who did and did not enroll in the trial using SAS version 9.4. Statistical significance was computed using Fisher exact test for categorical variables and Mann-Whitney for discrete ordinal variables and continuous variables. A *t* test was used to compare with Mann-Whitney *P* values as a check, and the results were similar except for distance to clinic. Due to outliers for distance to clinic, we report the medians. To compare agreement between the EHR and the study survey for specific comorbidities, we used the prevalence and bias adjusted kappa [50].

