### Randomization

Individuals were randomized 1:1 to IVR-T intervention or usual care using block randomization with blocks of 4. A randomization table was generated by the study statistician (SX) using SAS software. The study coordinators were blinded to the randomization sequence.

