### Study Visits

Participants complete in-person baseline, 6-month, and 12-month visits. At each visit, blood pressure measurements are collected and participants complete a survey. Blood pressure is measured in a standardized fashion during the research visits, using an Omron HEM 907XL IntelliSense Professional Digital Blood Pressure Monitor (an automated sphygmomanometer) [30]. After a 5 min waiting period, blood pressures are taken 3 times, 30 seconds apart. The average of the second and third blood pressures is used. The baseline survey can be self-administered or participants can request assistance from study coordinators. The baseline survey includes questions about general health, blood pressure treatment, adherence to blood pressure medications [31], comorbidities, perceived health competence (adapted from Smith et al [32]), depression (Patient Health Questionnaire-2) [33], discrimination (adapted from several sources [34-36]), health literacy and numeracy (adapted from Brega et al [37]), exercise and diet [38], demographics, and socioeconomic status and social needs (see Multimedia Appendix 2). The 6-month and 12- month visit surveys contain a subset of the questions from the baseline survey, with additional questions about attitudes toward the intervention. Survey answers and other study data are managed using REDCap software. Participants receive US $20 gift cards for each visit.

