### Endpoints

The primary outcome of the trial is the change in systolic blood pressure between baseline and 12-month research visits, comparing participants receiving the IVR-T intervention with those in usual care. Secondary outcomes are change in diastolic blood pressure between baseline and 12 months, self-reported adherence, and the proportion of missed clinic appointments.

The primary medication adherence measure is the self-reported Voils instruments administered at baseline and during both follow-up surveys [31,40-42]. The measure has 3 questions about the extent of nonadherence over the previous 7 days; the 5 response options range from missing medication “none of the time” to missing medication “all of the time.” If 1 or more items suggest nonadherence, 21 questions probe reasons for nonadherence; the 5 response options for each question range from being “not at all” a reason for nonadherence to being “very much” a reason. In prior studies, Cronbach alpha for the 3 “extent” items was .84, and the scale correlated significantly with systolic blood pressure and diastolic blood pressure [40]. Although it would have been ideal to corroborate this measure with pharmacy refill adherence or pill counts, FNCH clients use multiple pharmacies that preclude comprehensive assessment of refill adherence [43], and performing regular pill counts was not feasible.

The measure of visit adherence is the proportion of scheduled appointments that are kept, missed, or canceled. This measure is assessed using the FNCH EHR and calculated as a proportion of all visits scheduled during the period from enrollment to the end of follow-up. This is a standard measure in interventional trials to improve appointment keeping [11]. All 3 visit outcomes (kept, missed, and canceled) are important from an operational perspective, as timely visit cancellations allow FNCH to schedule other clients.

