### Power

Our initial target sample size for this study was 512, based on the following assumptions: (1) 1800 individuals in the FNCH hypertension registry, (2) 36% of eligible FNCH clients would agree to enter the study, and (3) 80% of those would complete the trial. This would have yielded 80% statistical power to detect a 5 mmHg reduction in systolic blood pressure with a Cronbach alpha of .05 and estimated SD in systolic blood pressure of 18 mmHg [51].

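### As ordinarily read, the primary mixed model estimates a separate baseline SBP mean in each arm; a common baseline mean or a baseline covariate would give a more precise 12-month contrast at no data cost

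*Protocol article*

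**What the plan says.** Under Endpoints, "The primary outcome of the trial is the change in systolic blood pressure between baseline and 12-month research visits", compared between arms. Under Study Visits, "Participants complete in-person baseline, 6-month, and 12-month visits".

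The Analysis Plan takes repeated SBP values as the response of a linear mixed model. It continues: "For each group, the changes from baseline at 6 and 12 months after randomization can be obtained after the linear mixed model is fit", and then: "Then, we will contrast the changes from baseline between the 2 groups to assess the influence of IVR-T intervention". DBP is handled in the same way. The section does not mention baseline SBP as a covariate. It also does not say whether the arms share one baseline mean or have one each.

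Under Randomization, "Individuals were randomized 1:1 to IVR-T intervention or usual care using block randomization with blocks of 4". Eligibility and Recruitment places the baseline blood pressure measurement before randomisation.

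Under Power, "Our initial target sample size for this study was 512". The section Baseline Characteristics of the Study Cohort reports that 295 were enrolled, that the recruitment pool was exhausted, and that the detectable difference at 80% power is now 6.5 mmHg.

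**The concern.** Baseline SBP is one of the modelled outcomes, and each arm's change is measured from baseline. The usual way to fit such a model is with group, visit and group-by-visit terms, which gives each arm its own baseline mean. The 12-month contrast is then a difference in differences, and with complete data it equals the difference between the two mean changes.

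Baseline is measured before 1:1 randomisation, so the two true baseline means are the same number. Estimating them separately carries the chance baseline difference at full weight into the treatment estimate. A model that uses the known equality, or that conditions on baseline, removes this avoidable noise.

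Precision is at stake. The trial enrolled 295 against a target of 512 and cannot recruit more from its pool. Baseline SBP is already collected by design, so the gain needs no new data.

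**Working it through.** **Inputs from the article.** Final N 295, allocated 1:1. Planned completion 80%, SD 18 mmHg, significance level .05 and 80% power (Power). Observed baseline SBP SD 19.5 mmHg (Table 4).

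**Assumptions, not in the article.** Correlation ρ between visits, shown over a range. Compound symmetry. 10% missing at 6 months. A two-sided test, which reproduces the article's figures.

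**1. The article's own power figures.** The multiplier is 1.960 + 0.842 = 2.802.
- Target: 204 per arm for 5 mmHg at SD 18, so 408 completers, and 408/0.8 = 510 (stated 512).
- Final sample: 295 × 0.8 = 236 completers. The detectable difference is 2.802 × 18 × √(4/236) = 6.57 mmHg (stated 6.5).

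Both reproduce. They use the SD of SBP itself and take no credit for baseline adjustment.

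**2. One follow-up visit, complete data.**
- Change contrast: variance = 2σ²(1−ρ) × 4/N.
- Baseline-adjusted or common-baseline contrast: variance = σ²(1−ρ²) × 4/N.
- Ratio, adjusted to change = (1+ρ)/2, so the information lost is (1−ρ)/2.

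The ratio is below 1 for every ρ below 1, so the direction needs no assumption about ρ. The loss is 35% at ρ = 0.3, 25% at 0.5, 15% at 0.7 and 10% at 0.8.

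**3. Three visits with dropout.** The 12-month arm effect was taken from the inverse of the information matrix ΣnX′V⁻¹X. There are 147.5 per arm: 80% have all three visits, 10% baseline and 6 months only, and 10% baseline only. The free-baseline model has six mean parameters and the common-baseline model has five. The table uses SD 19.5; the variance ratios do not depend on the SD.

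| ρ | Variance ratio (common / free) | Information lost | 80%-power difference, free → common (mmHg) |
|---|---|---|---|
| 0.3 | 0.70 | 30% | 8.1 → 6.8 |
| 0.5 | 0.79 | 21% | 6.9 → 6.1 |
| 0.7 | 0.87 | 13% | 5.4 → 5.0 |
| 0.8 | 0.92 | 8% | 4.4 → 4.2 |

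At ρ = 0.5 the standard errors are 2.46 (free) and 2.18 (common). Then 2.802 × 2.46 = 6.9 and 2.802 × 2.18 = 6.1 mmHg. Power at 6.5 mmHg rises from 75% to about 85%. With the planning SD of 18 instead, the detectable differences are 6.37 and 5.65 mmHg.

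**4. Sample-size equivalent.** At ρ = 0.5 the unrounded ratio is 0.787, and 295/0.787 = 375. The shortfall is 512 − 295 = 217 and the gain is 375 − 295 = 80, so 80/217 = 37% is recovered. With the rounded ratios in the table, ρ = 0.3 gives 295/0.70 = 421, a gain of 126 (58%), and ρ = 0.7 gives 295/0.87 = 339, a gain of 44 (20%).

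**The case against.** The strongest reply is that the article never states a free baseline mean per arm. A constrained longitudinal model also has baseline in the response vector, and its result is also reported as a contrast of changes from baseline, so the quoted sentences fit the proposed remedy too. An article may leave this detail to a fuller plan. This stands in part: the free-baseline model is the ordinary reading, not a stated choice, and if baseline is already constrained the loss is zero. It does not dispose of the point, because the article describes how the estimate is built and omits the one element that would make it efficient.

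Four stronger readings are tempting, and the documents do not support them.
- A reader might infer that raw change scores are analysed. They are not: the changes "can be obtained after the linear mixed model is fit and all coefficients are estimated", so they are model-based.
- A reader might infer bias from chance baseline imbalance or regression to the mean. Under randomisation the contrast is unbiased and its type I error is valid; chance imbalance is already reflected in its standard error.
- A reader might fix the loss at 20 to 25%. That needs ρ of about 0.5 to 0.6, which the article does not state. The planning SD of 18 equals the SD of a change only at ρ = 0.5, but this coincidence does not establish the correlation.
- A reader might conclude that adjustment offsets most of the recruitment shortfall. At ρ = 0.5 it recovers about 37%.

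The 6.9 mmHg figure should also not be set against the article's 6.5 as a cost of baseline handling. It partly reflects the use of SD 19.5 instead of 18.

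**Conclusion.** The point holds as one of efficiency. The planned contrast is valid and matches the stated endpoint, but on the ordinary reading it is less precise than a model that uses the equality of baseline means under randomisation. The direction holds for every correlation below 1. The size is conditional: it rests on compound symmetry, the assumed 6-month missingness, the article's 80% completion and an unknown correlation. Over correlations of 0.3 to 0.8 the loss runs from about 30% down to 8%. Confidence is moderate, because the wording also admits a constrained model. The change is worth making because the trial fell well short of its target and the gain needs no further participants or measurements.

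**What to change.** Before unblinded analysis, state one of the following in the model specification:
- the same linear mixed model with a common baseline mean: visit as a categorical factor, arm-by-visit terms at 6 and 12 months only, and unstructured covariance; or
- a mixed model for 6- and 12-month SBP with baseline SBP as a covariate.

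In either case, name the 12-month arm effect as the primary estimate, and specify DBP in the same way. The endpoint can still be reported as a difference in change from baseline. The cost is one line of specification and no extra data. If the full plan already constrains or adjusts for baseline, one clarifying sentence in the article is enough.

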**Household income, n (%)^a^**		
	Nothing	27 (10.2)
	Less than US $10,000	75 (28.3)
	US $10,000 to US $14,999	50 (18.9)
	US $15,000 to US $19,999	26 (9.8)
	US $20,000 to US $24,999	35 (13.2)
	US $25,000 to US $34,999	22 (8.3)
	US $35,000 to US $49,999	17 (6.4)
	US $50,000 to US $74,999	10 (3.8)
	More than US $75,000	3 (1.1)
Household income, mean (SD)		US $17,170 (17,058)

^a^Numbers do not sum to 295 due to missing values. The number of missing values are as follows: marital status=1, education=1, household income=30.

Self-reported race/ethnicity differed somewhat from race/ethnicity data from the EHR, although the overall agreement was 90.2% (266/295). The study cohort was 25.1% (74/295) AI/AN and 51.9% (153/295) Hispanic. Among the AI/AN participants, 8 (10.8%) also identified as Hispanic. Almost all participants reported having hypertension (94.5%), whereas 79.8% reported taking blood pressure medication. Only 17.4% had a home blood pressure monitor. Nearly all individuals in the intervention group (144/148, 97%) opted to receive a blood pressure monitor as part of the study intervention. Over one-third (39.0%) had a baseline blood pressure greater than or equal to 140/90 mmHg. Our self-reported medication adherence rate was 36.4%. Concordance between the medical record and the survey was relatively good for most chronic health conditions, with prevalence and bias adjusted kappa for diabetes, CVD, chronic kidney disease, and depression of 0.81, 0.71, 0.73, and 0.55, respectively.

Over three-quarters of the sample reported a poor diet. Our study cohort reported poor general health, with only 46% reporting good or better health. Self-reported socioeconomic status was low. Over one-third of participants had less than a high school education, and over one-quarter of individuals were unemployed or unable to work. Over one-third of participants reported annual household incomes of less than US $10,000, with a mean annual household income of US $17,170 and median household income of US $12,500. Basic resource needs were very common. High percentages of participants reported they did not always have enough money to buy food, health care, or utilities.

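### The graded three-item adherence scale appears set to be analysed as a yes/no status, which would hide change among the 63.6% classed as nonadherent at baseline

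*Protocol article*

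**What the plan says.** The Endpoints section describes a graded instrument: "The measure has 3 questions about the extent of nonadherence over the previous 7 days", and "the 5 response options range from missing medication" at none of the time up to all of the time. It backs the instrument with scale-level evidence: "Cronbach alpha for the 3 “extent” items was .84", plus correlation of the scale with systolic and diastolic pressure. The measure is taken at baseline and at both follow-up surveys.

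The Analysis Plan keeps systolic pressure and "diastolic blood pressure (a secondary outcome variable) as continuous variables" in linear mixed models. For the rest it says: "We also plan to analyze the secondary outcomes missed appointment and medication adherence status using nonlinear mixed models".

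The results on this scale are all in adherent/not form. Table 4 gives 82 (36.4%) adherent with 8 missing. The text after Table 3 says "Our self-reported medication adherence rate was 36.4"%, and the Discussion sets that rate against 63% in a cited study of US veterans. No mean or distribution of the graded score appears.

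The only text near a cut-off is a questionnaire routing rule in Endpoints: "If 1 or more items suggest nonadherence, 21 questions probe reasons for nonadherence".

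**The concern.** The measure described and the variable named for analysis do not match. Internal consistency is a property of a multi-item score. The analysis variable is called a status, shares a sentence and a model class with missed appointments, and is set apart from the outcomes kept continuous. Table 4 reports health literacy, numeracy and perceived health competence as mean (SD), but this scale only as a count and percentage.

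The Eligibility and Recruitment section names people who do not take their medication reliably as a specific target of the intervention. They make up 143/225 = 63.6% of those scored at baseline. The intervention sends weekly motivational messages and monthly refill reminders, so partial improvement is a plausible effect. A yes/no outcome counts such improvement only when a participant crosses the cut-off. Adherence is also the secondary outcome that would help explain a blood pressure result, and the trial enrolled 295 against a target of 512, so it has little information to spare.

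**Working it through.** **1. Reproduce the stated rate.** Table 4 has 233 participants taking blood pressure medication, 82 adherent and 8 missing on the scale. 82/(233 − 8) = 82/225 = 36.4%, which matches. Other denominators do not: 82/295 = 27.8%, 82/287 = 28.6%, 82/233 = 35.2%. The split is therefore p = 0.3644 adherent and 1 − p = 0.6356 nonadherent.

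**2. Information kept by the split.** Under proportional odds, the information on the log odds ratio is proportional to 1 − Σpᵢ³ over the response levels (Whitehead).

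- Yes/no: 1 − p³ − (1 − p)³ = 3p(1 − p) = 3 × 0.3644 × 0.6356 = 0.695.
- Graded, with the adherent group as one level and the nonadherent spread as finely as possible: at most 1 − p³ = 1 − 0.048 = 0.952.
- Lowest efficiency of yes/no: 0.695/0.952 = 0.730, so the loss is at most 27%.

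The article gives no distribution within the nonadherent group, so a range of spreads is assumed. Three five-level items give a sum with 13 values, which leaves 12 if the best value alone is adherent. Power is for N = 180 and an odds ratio of 2.0 (step 3).

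| Assumed spread of the nonadherent 63.6% | Efficiency of yes/no | Loss | Power, graded |
|---|---|---|---|
| Even over 12 levels | 0.732 | 26.8% | 72.5% |
| Even over 4 levels | 0.743 | 25.7% | not computed |
| 50/30/15/5 | 0.762 | 23.8% | 71.1% |
| 65/22/9/4 | 0.791 | 20.9% | 69.9% |
| 80/15/4/1 | 0.848 | 15.2% | 67.9% |

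Example, 50/30/15/5: the nonadherent levels are 0.318, 0.191, 0.095 and 0.032. Their cubes sum to 0.040. Graded information is 1 − 0.048 − 0.040 = 0.912, and 0.695/0.912 = 0.762.

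**3. Power.** Assumptions: 225 × 80% completion (the rate in the Power section) = 180, or 90 per arm; two-sided 5%; one comparison at one visit; odds ratio 2.0, chosen for illustration.

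- Adherent odds: 82/143 = 0.573. Doubled: 1.147. So 36.4% becomes 1.147/2.147 = 53.4%.
- Yes/no, two-proportion test: the difference is 0.170, with standard error 0.0742 under the null and 0.0731 under the alternative. (0.170 − 1.96 × 0.0742)/0.0731 = 0.33, so power is 63%.
- Graded: Φ(ln 2 × √[(180/12)(1 − Σp̄ᵢ³)] − 1.96), with p̄ᵢ averaged over arms. For 50/30/15/5, 1 − Σp̄ᵢ³ = 0.879, so 0.693 × √13.18 − 1.96 = 0.557 and power is 71%.
- Like with like: the same formula for yes/no uses 3 × 0.449 × 0.551 = 0.742, so 0.693 × √11.13 − 1.96 = 0.353 and power is 64%.

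With all 225 retained, power is 73% for yes/no against 77-82% graded.

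**The case against.** The article never says that the follow-up variable is binary. A nonlinear mixed model can be ordinal, the 36.4% is a baseline description, and scoring details of a secondary survey outcome are commonly left to an analysis plan. This stands as a limit on certainty: yes/no is the natural reading, not a stated fact. It does not dispose of the point, because the article does name an analysis variable, and that name and all the reporting point away from the graded scale.

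Reporting a rate from this scale has a precedent among the article's own sources, as the Discussion's comparison with veterans shows. That also stands. It is a reason to keep the percentage, and a reason not to claim that the cited validation fails to cover a dichotomised version, which cannot be checked here.

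Two stronger readings are tempting:

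- A reader might infer that adherent requires the best answer on all three items, so that moving from missing medication all of the time to missing it rarely would count as no change. The routing rule suggests that cut-off but governs only when the reasons questions are asked. No outcome cut-off is stated.
- A reader might infer that a quarter of the information is lost outright. A loss of 27% is the ceiling of the calculation above, and the actual loss depends on a score distribution that the article does not give. If the nonadherent cluster near the boundary, or the effect falls there, the yes/no status captures much of the gain.

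**Conclusion.** The point holds as a cheap improvement to a secondary outcome. On the natural reading, a graded measure will be analysed as yes/no, and whatever the cut-off, change within the 63.6% classed as nonadherent would go unseen. The information lost is about 15-27%, equivalent at an odds ratio of 2.0 and N = 180 to power of about 63% rather than 68-73%.

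These figures assume proportional odds, a single-visit comparison and the spreads in the table. They also treat the adherent group as one level. If the cut-off admits several levels, graded information can approach 1 and the ceiling rises to 1 − 0.695 = 30.5%. More extreme clustering than 80/15/4/1 would take the loss below 15%. The article claims no power for adherence, and the systolic pressure analysis and its stated power are untouched.

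**What to change.** Name the graded score of the three extent items as the adherence outcome. Analyse it with an ordinal (cumulative logit) mixed model over baseline, 6 and 12 months, with the between-arm contrast at 12 months as the main adherence result. An ordinal model copes with a pile-up of answers at the best score. Keep adherent yes/no as a supportive summary, state its cut-off, and use it for comparison with the published rate. If an ordinal analysis was already intended, replacing the word status with the name of the score settles the matter.

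The cost is analysis wording only, because the items are already administered at all three visits. The downsides are that an odds ratio or score is less readable than a percentage, which the supportive summary offsets, and that the model adds a proportional-odds assumption that should be checked. The change should be fixed before adherence is compared by arm.
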